##### Qualitative analysis

Based on the narratives of the semidirective interviews, a content analysis will be performed, with several chronological phases (reanalysis, operation of equipment, and interpretation) (Bardin, 2013). According to a new method developed by Renz et al. (2018), two data analyses (i.e., manual and computer based) will be combined to enhance the trustworthiness of the results. The first method is based on a manual content analysis (Graneheim et al., 2017). Three authors (EL, [name], and [name]) will first look at the apparent messages through a repeated reading of the transcripts to achieve immersion and obtain a sense of the whole. In addition, this first reading will allow us to define thematic and formal categories relevant for later coding speeches. Units of meaning will then be independently identified, categorized and put into relation to identify axes of transversal meanings. This process will allow us to classify the elements and to emit a simplified representation of the raw data. The second method will use a computer-based content analysis, through the NVivo software, and will be performed by another author (MV). NVivo is a computer-assisted qualitative data analysis software that allows for qualitative inquiry beyond the coding, sorting and retrieval of data (Wong, 2008). The benefits of using NVivo are outlined in terms of facilitating teams of researchers to systematically and rigorously synthesize qualitative data.

Finally, the results issued from the two methods will be grouped and organized through a coding scheme.

### Funding Sources and Ethical Approval

The SUPPORT-S study is funded by the Scientific Research Committee from the Centre Hospitalier le Vinatier and University Lyon 2. The study received ethical approval from the Ethical Review Board Sud-Est IV of Clermont-Ferrand (registration number 2019/CE67).

## Expected Results

Although the impact of PUS on mental health professionals and social workers has been well described, the SUPPORT-S study will be the first to evaluate the effectiveness of a postvention program for professionals exposed to PUS. The mixed method and action research design will allow us to collect both in-depth qualitative and quantitative data on the effectiveness of the implementation of the SUPPORT program. The multidisciplinary approach through the collaboration of researchers and clinicians from different disciplines and theoretical backgrounds is another strength of the study, as it will improve the strength and generalizability of our conclusions. While previous studies have relied on retrospective data collection through large surveys or qualitative interviews (e.g., individual interviews or focus-groups), the longitudinal design of the current study will offer new insights and perspectives on PUS and its impact on professionals and institutions.

Our study protocol has several limitations. First, the non-controlled design prevents us from making definitive inferences on the effectiveness of the program. The use of a research-action approach may also limit the representativeness of the sample, induce selection biases and limit the ability to avoid misinterpretation in the researchers’ conclusions. Second, the SUPPORT-S study is a monocentric study performed in the French context. This setting may impede the generalizability of our conclusions and results, due to the particularities of the French health system and social policies. Finally, the small number of local implementations (5) may limit the power of our results and conclusions. However, the following four main bias limitations will be used in the SUPPORT-S study: (a) triangulation, (b) randomization, (c) saturation, and (d) participatory approach. *Triangulation* refers to the use of multiple methods or data sources in qualitative research to develop a comprehensive understanding of phenomena (Patton, 1999; Carter et al., 2014). Denzin (1978) and Patton (1999) identified the following four types of triangulation: (a) method triangulation, (b) investigator triangulation, (c) theory triangulation, and (d) data source triangulation. The four types of triangulation will be ensured in the SUPPORT-S study through the mixed method and action research design (method and data source triangulation) and the involvement of researchers from different disciplines and theoretical backgrounds (theory and investigator triangulation). An intramethod triangulation will also be added through the two methods of content analysis previously described in the paragraph on qualitative analysis. The *randomization* of professionals to participate in individual semidirected interviews will limit the selection bias by randomly ensuring the representativeness of the sample and avoiding the biased selection of, for instance, more motivated professionals. *Saturation* is used in qualitative designs as a criterion for discontinuing data collection and analysis (Saunders et al., 2018). According to the taxonomy developed by Saunders et al. (2018), the following four types of saturation are defined: (a) theoretical saturation (i.e., the development of theoretical categories), (b) inductive thematic saturation (i.e., the emergence of new codes or themes), (c) *a priori* thematic saturation (i.e., the degree to which identified codes or themes are exemplified in the data), and (d) data saturation (i.e., the degree to which new data repeat what was expressed in previously collected data). The saturation used in the SUPPORT-S study will focus on the data saturation and the inductive thematic saturation. The *participatory approach* is an effective means to limit the misinterpretation of the collected data by the researchers. The involvement of participants in the restitution process promotes the ability to adjust the program as well as the conclusions issued from the research through their direct comments of the results.

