## IntroductIon

Exposure to patient or user suicide (PUS) has been identified as a frequent and challenging occupational hazard for mental health and social work professionals (Gulfi et al., 2010; Séguin et al., 2014; Castelli Dransart et al., 2017; Leaune et al., 2019a). For instance, between 51 and 82% of psychiatrists (Castelli Dransart et al., 2017), 46.9% of psychiatric trainees (Leaune et al., 2019a), between 22 and 39% of psychologists (Castelli Dransart et al., 2017), 55% of nurses (Takahashi et al., 2011) and 33% of social workers (Jacobson et al., 2004) will experience PUS during their training or career. Cerel et al. (2014) identified a “continuum of survivorship” after suicide, distinguishing those who are exposed to, affected by, or bereaved long-term or short-term by suicide. Considering PUS, all the members of the staff may encounter high levels of psychological distress and professional difficulties in the aftermath, including emotional, traumatic, and professional impacts (Séguin et al., 2014; Castelli Dransart et al., 2017; Leaune et al., 2019a, b). The emotional impact frequently includes shock, guilt, sadness, anger, failure, shame, and anxiety. Stress and traumatic reactions are also reported, including acute stress and posttraumatic stress disorders. Regarding professional impact, PUS may challenge the feelings of self-confidence and professional competence. A fear and avoidance of suicidal individuals, an impairment in professional decision-making or a decrease in work performance are notably reported. Some of the exposed professionals may also experience grief reactions or disenfranchised grief, i.e., a grief that is denied the right to exist because the impact of the loss is not recognized by peers, superiors or society (Doka, 1989). The majority of professionals will positively manage the impact of PUS through professional growth and encounter it as a learning and beneficial experience. In contrast, a minority of professionals will show high levels of impacts, with negative personal and professional outcomes. The term “second victims,” proposed to designate professionals exposed to adverse medical events in patients, has thus been used in the case of professionals impacted by PUS (Scott, 2019). The negative impact of PUS is significantly associated with a closeness to the deceased, a high level of the professional–client relationship and a lack of support and training. Castelli Dransart et al. (2015) notably reported that the lack of support in the aftermath was a risk factor for higher traumatic impact in the aftermath of PUS.

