#### Stage 3: Late Detection and Counseling

The third stage of the program seeks to perform late detection and counseling support for professionals who are strongly affected or traumatized by exposure to PUS. Those who feared attending the team-based intervention stage may notably receive individual debriefing during this stage. Stage 3 aims to promote the return to normal functioning in the institution, at both the individual and organizational levels. When stage 3 has not been effective in ensuring the recovery among professionals, a fourth stage can be added to properly support the impacted team.

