#### Study Design

SUPPORT-S is a mixed method collaborative and participatory action research study, including a total of five SUPPORT interventions over a total of 15 months (Figure 2). SUPPORT-S seeks to evaluate both the effectiveness of the program from the perspective of professionals who receive the intervention (i.e., participants) and those who deliver it (i.e., providers) through an iterative participatory process.

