##### Qualitative data

An *ethnographic observation* of the local implementation of the SUPPORT program will be performed by social sciences researchers ([name], MV, and [name]) to collect in-depth observational data on the implementation of the program. The observation will notably focus on the reaction of the professionals exposed to PUS, and how they manage and experience the implementation of the SUPPORT program. The interactional processes between professionals delivering the program will also be examined.

For each intervention, five exposed professionals will be randomly selected to participate in an *individual semistructured interview* at the end of the program. The semistructured interviews will last between 30 and 60 min and will be performed by one or two social researchers ([name], MV, and [name]) in the workplace of participants. The participants will be interviewed regarding their individual experience of the SUPPORT program, including: how they perceived the program for themselves and for their team, which mechanisms led to its effectiveness and how the program could be improved. The content of the interview will be recorded and anonymized.

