##### Estimated number of participants

The inclusion of 150 exposed professionals is expected for the collection of quantitative data. Considering the five local implementations of the SUPPORT program throughout the SUPPORT-S study, the inclusion of 150 exposed professional is needed to observe a 30% decrease in the mean IES-R score between T0 and T1 with a 90% statistical power.

Of them, a total of 25 professionals will participate in the semistructured interviews. According to previous qualitative studies on professionals’ experiences of adverse events in which similar (Ullström et al., 2014; Ferrús et al., 2016) or lower (Chan et al., 2018; Kable et al., 2018) samples were included, the inclusion of 25 professionals in semidirected interviews should provide sufficient saturation for the representativeness and reliability of the data. However, the sample of participants in semidirected interviews could be increased if saturation is not reached.

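### Drawing five interviewees per team at random prevents hand-picking but does not ensure a representative sample, and one of the interview topics presumes that the program worked

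*Protocol article*

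**What the plan says.** All references are to the protocol article.

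- **Selection (Qualitative data).** "For each intervention, five exposed professionals will be randomly selected to participate in an" individual semistructured interview at the end of the program. No stratification or quota is described.
- **Numbers.** Study Design describes the study as "including a total of five SUPPORT interventions over a total of 15 months". Under Estimated number of participants, "The inclusion of 150 exposed professionals is expected for the collection of quantitative data", and 25 of these are interviewed.
- **Claimed property (Expected Results).** Randomization is listed as one of four means of limiting bias. It is said that it "will limit the selection bias by randomly ensuring the representativeness of the sample" and that it avoids a selection tilted toward, for example, more motivated staff.
- **Topics (Qualitative data).** Interviewees are asked how they perceived the program for themselves and for their team, then "which mechanisms led to its effectiveness and how the program could be improved".
- **Who is strongly affected (Introduction).** The article expects that "a minority of professionals will show high levels of impacts, with negative personal and professional outcomes". It gives no percentage.
- **Use of the data (Table 1).** Each cycle ends with an adaptation of the program before the next implementation. The interviews feed it together with observation, activity analysis with the providers, the questionnaires and a workshop with participants and providers.

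**The concern.** The primary objective is to improve the program, and it is revised team by team. Its detection and counseling stages exist mainly for staff who are strongly affected. Under Stage 3: Late Detection and Counseling the article adds: "Those who feared attending the team-based intervention stage may notably receive individual debriefing during this stage". These are the people whose account of where the program falls short is most informative. An unstratified draw of five can easily contain none of them.

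The article nevertheless credits the draw with securing representativeness, so a reader of the results could take a cycle's five interviews as covering the range of reactions in the team.

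The second half of the concern is the wording of a topic. Asking which mechanisms produced effectiveness treats benefit as established. The same Expected Results section says that the uncontrolled design does not allow definitive inference on effectiveness. A question framed this way invites favorable answers in the data that serve the primary objective.

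**Working it through.** **Inputs**

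- Interviews per team: n = 5 (Qualitative data).
- Teams, that is cycles: 5 (Study Design).
- Included staff: 150 (Estimated number of participants).
- Average team size: N = 150/5 = 30. This is derived; actual team sizes are not stated.
- Strongly affected staff per team: K. The article gives no figure, so K is an assumption, taken here as 3 to 9 of 30 (10% to 30%).

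**The plan's own figure.** 5 interviews × 5 teams = 25, which agrees with the stated total.

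**One cycle.** Under a random draw without strata, the probability that none of the five is strongly affected is hypergeometric:

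P0 = C(N − K, 5) / C(N, 5), with C(30, 5) = 142,506.

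- K = 3: C(27, 5) = 80,730, so P0 = 80,730/142,506 = 0.567
- K = 4: C(26, 5) = 65,780, so P0 = 0.462
- K = 6: C(24, 5) = 42,504, so P0 = 0.298
- K = 9: C(21, 5) = 20,349, so P0 = 0.143

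**Five cycles**, treated as independent with the same N and K. The expected number of cycles with no such interviewee is 5 × P0. The probability of at least one such cycle is 1 − (1 − P0)^5. The probability that all 25 interviews miss the group is P0^5.

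| Assumed prevalence | P0, one cycle | Expected cycles of 5 | At least one cycle | All 25 interviews |
|---|---|---|---|---|
| 10% (3 of 30) | 0.567 | 2.8 | 0.985 | 0.058 |
| 13% (4 of 30) | 0.462 | 2.3 | 0.955 | 0.021 |
| 20% (6 of 30) | 0.298 | 1.5 | 0.830 | 0.002 |
| 30% (9 of 30) | 0.143 | 0.7 | 0.537 | 0.0001 |

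**Sensitivity.** Team size matters little. At 10%, P0 is 0.55 for N = 20 and 0.58 for N = 50. At 20%, it is 0.26 for N = 15 and 0.31 for N = 50. Prevalence matters a great deal: at 40% (12 of 30), P0 falls to 8,568/142,506 = 0.06.

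**Topics, set side by side.** Three are listed: how the program was perceived, which mechanisms made it effective, and how it could be improved. The first and third leave room for criticism. Only the second presupposes success.

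**The case against.** The strongest reply has four parts.

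1. **Interviews are not the only source.** Table 1 has each revision follow from proposals made at the sharing workshop, informed also by observation, activity analysis and the T0 and T1 questionnaires. Strongly affected staff who complete the questionnaires are visible in a cycle's data without being interviewed. This stands. A reader might infer that revisions could go ahead without hearing from these staff at all, and the article does not support that. It is equally true that nothing described secures this group's voice at the workshop. The activity analysis uses film of the stage 2 session with comments from providers, and the section Mixed method evaluation assigns depth of understanding to the qualitative data.

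2. **The size rests on an assumed prevalence.** This stands. A reader might infer that about half the cycles would lack such an interviewee, but that needs a prevalence of about 10% to 13%, which the article does not give.

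3. **Over the whole study the group is very likely to be interviewed.** This stands too. A complete miss in 25 has probability 0.06 at 10%, and the sample may be enlarged if saturation is not reached. A claim that saturation would be declared with no interview from this group is therefore not supported. It does not help an individual cycle, since the program is adapted before the next team.

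4. **An article condenses the full protocol.** Strata and a fuller interview guide may exist elsewhere, and random selection has a legitimate stated purpose. For that reason the absence of strata is not itself the fault. What the article does state is the representativeness claim and the leading topic. A reader might also infer that the whole topic list presumes success, but two of the three topics do not.

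**Conclusion.** The point holds in a limited form. Random selection of five per team protects against hand-picking, but it does not ensure representativeness, and the article says that it does.

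With teams of about 30, no strata, all those drawn agreeing, and 10% to 30% of staff strongly affected, a given cycle interviews none of them with probability about 0.57 to 0.14. At least one of the five cycles does so with probability about 0.98 to 0.54. If strongly affected staff decline interviews more often than others, the probabilities are higher; if they are more common than assumed, lower. The weakness lies in single cycles and not in the pooled 25 interviews.

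One of the three listed topics is leading. Neither matter invalidates the study. Both are inexpensive to correct and bear on the data used for the primary objective.

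**What to change.** 1. **Selection.** Keep five randomly drawn interviews per team, but stratify the draw by the IES-R score at T0, using the cut-off of 24 that the section Quantitative data already defines. Draw one or two of the five places at random from staff above the cut-off, where such staff agree, and the rest from the others. In any team with someone above the cut-off who agrees, the chance of interviewing none of that group becomes zero. The share of staff above 24 is not given and may differ from the strongly affected minority of the Introduction, so the guarantee applies to the group as defined by the cut-off. Attendance at stage 2 is not a suitable stratum: it is not among the listed data, and reserving places for non-attenders would not secure a strongly affected interviewee.
2. **Topic.** Replace the effectiveness topic with a neutral one: what, if anything, helped, made no difference or made things worse, stage by stage.
3. **Wording.** In Expected Results, replace the claim about representativeness with a statement that the draw avoids hand-picking and is stratified by initial impact.

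**Cost.** No extra interviews and a minor edit to the interview guide. The person making the draw needs the coded T0 score, which should be kept from the interviewers. The interview sample is no longer proportional to the team, so counts of themes should not be read as team proportions.

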
## Conclusion

Health and social work professionals are frequently exposed to PUS and may encounter several ranges of emotional, traumatic or professional impacts in the aftermath. The lack of support in the aftermath of PUS has been reported by a high proportion of exposed professionals, indicating the urgent need to implement and evaluate innovative programs dedicated to facilitating recovery and preventing negative health outcomes after a PUS. The SUPPORT program is a postvention program designed to provide comprehensive, adaptative and effective support to professionals impacted by a PUS. The SUPPORT-S study is a mixed method collaborative and participatory action research project aiming to (1) improve the design of the SUPPORT program, (2) evaluate the effectiveness of the SUPPORT program to buffer the emotional, traumatic and professional impacts and to improve the perceived social support for professionals exposed to PUS and (3) provide more insights into the consequences of PUS on both professionals and organizations. The simultaneous and complementary collection and analysis of qualitative and quantitative data will offer an in-depth evaluation of the program’s implementation and effectiveness. The action research design will also improve the limitation of biases and improve the generalizability of the conclusions. The results of the study will allow us to disseminate an effective postvention program for professionals and institutions encountering PUS.

## Ethics Statement

The studies involving human participants were reviewed and approved by Comité de Protection des Personnes Sud-Est VI. The patients/participants provided their written informed consent to participate in this study.
